## Abstract

**Background:**

There has been immense interest and debate regarding the effectiveness of antibiotic treatment for chronic low back pain. Two randomised controlled trials have examined the efficacy of antibiotics for chronic low back pain with disc herniation and Modic changes, but have reported conflicting results. The aim of this double-blind, randomised, placebo-controlled trial is to determine the efficacy of antibiotic treatment in a broader patient subgroup of chronic low back pain with disc herniation and investigate whether the presence of Modic changes predicts response to antibiotic therapy.

**Methods:**

One hundred and seventy individuals with chronic low back pain will be recruited through hospital and private medical and allied health clinics; advertising in national, community and social media; and posting of flyers in community locations. They will be randomly allocated to receive either amoxicillin-clavulanate (500 mg/125 mg) twice per day for 90 days or placebo. The primary outcome measure of pain intensity will be assessed using the Low Back Pain Rating scale and a 100-mm visual analogue scale at 12 months. Secondary measures of self-reported low back disability and work absence and hindrance will also be examined, and an economic analysis will be conducted. Intention-to-treat analyses will be performed.

**Discussion:**

There is uncertainty about whether antibiotic treatment is effective for chronic low back pain and, if effective, which patient subgroup is most likely to respond. We will conduct a clinical trial to investigate the efficacy of antibiotics compared with placebo in individuals with chronic low back pain and a disc herniation. Our findings will provide high-quality evidence to assist in answering these questions.

**Trial registration:**

Australian New Zealand Clinical Trials Registry ACTRN12615000958583. Registered on 11 September 2015

**Supplementary Information:**

The online version contains supplementary material available at 10.1186/s13063-021-05728-1.

## Background

Low back pain is a major global health issue. It is not only the leading cause of disability worldwide [1], but evidence-based treatments are limited and only provide small to moderate benefits [2]. Recently, there has been enormous interest and controversy around a potential new treatment approach involving antibiotic therapy for a specific patient subgroup with chronic low back pain [3, 4]. The approach is based on the hypothesis that some individuals that sustain a disc herniation develop chronic low back pain due to a secondary, low-grade infection that develops in the disc [5]. This infection may result from a breach in the disc’s integrity allowing low virulent organisms that are commonly present on human skin to travel via the blood stream to the disc, resulting in infection, adjacent bone oedema (Modic change) and disabling back pain.

The first randomised controlled trial of antibiotic therapy by Albert et al. showed that amoxicillin-clavulanate (500/125mg) three times per day for 100 days was more effective than placebo for chronic low back pain with disc herniation and adjacent Modic type 1 changes (vertebral bone oedema) [6]. These findings were considered analogous to the discovery of *Helicobacter pylori* and the treatment of gastric ulcers, where a previously common, non-infectious condition was found to have an infective origin. While these results show promise for the prescribing of antibiotics for a specific patient subgroup with low back pain, commentaries in the BMJ highlight the importance of further research before a change in practice can be justified [3, 4]. More recently, a second clinical trial by Bråten et al. found that treatment with antibiotic therapy, amoxicillin (750 mg) 3 × per day for 3 months, did not provide a clinically important benefit in patients with chronic low back pain and Modic type 1 or 2 changes at the level of a previous disc herniation [7]. While these trials by Albert et al. and Bråten et al. provide contrasting results regarding the efficacy of antibiotic treatment for chronic low back pain, there are key differences in their methodology, including differences in the type of Modic changes examined and the type of antibiotic treatment prescribed, which may explain the disparity [6, 7].

We previously conducted a systematic review to comprehensively examine whether bacteria have a role in low back pain and to investigate the relationship between bacteria and Modic changes [8]. Our review found that bacteria are present in the spinal discs of people with back pain (undergoing spinal surgery), and there are a variety of bacteria present, including both *Cutibacterium acnes* (formerly known as *Propionibacterium acnes*) and *Coagulase-negative staphylococci*. We also found a relationship between the presence of bacteria and both low back pain with disc herniation and Modic changes associated with disc herniation. The findings of this systematic review and the previous clinical trials provide direction for future studies, including the need to further investigate the efficacy of a broad-spectrum antibiotic given the wide variety of bacteria identified, as well as the need to explore the defining clinical features of a patient subgroup, in particular disc herniation, which may benefit from antibiotic treatment.

Overall, while there is evidence for a role of bacteria in chronic low back pain, it remains unclear whether antibiotic treatment is effective for chronic low back pain and whether disc herniation with Modic changes represents a select target population, or whether all individuals with disc herniation may respond to antibiotics. We propose a double-blind, randomised, placebo-controlled trial to determine whether broad-spectrum antibiotic treatment (amoxicillin-clavulanate) is effective in reducing pain in individuals with chronic low back pain and disc herniation. Our secondary aims are to determine whether antibiotics are effective in reducing disability and work absence and hindrance and investigate whether the presence of Modic changes predicts those individuals more likely to respond to antibiotic therapy. A cost-effectiveness analysis will also be conducted. If found to be effective, the trial will provide high-quality evidence to support the use of antibiotics for chronic low back pain with disc herniation with or without Modic changes, a major area of unmet need. If we do not find amoxicillin-clavulanate to be effective, then our trial will provide strong evidence to consider it as an inappropriate approach in the management of chronic low back pain with disc herniation.

## Methods

### Study design

This study is a double-blind, randomised, placebo-controlled trial, with a two-arm, parallel group, superiority design. The trial was registered at the Australian New Zealand Clinical Trials Registry prior to recruitment (ACTRN12615000958583), and trial reporting will be guided by the Consolidated Standards of Reporting Trials (CONSORT) [9] and Standard Protocol Items: Recommendations for Interventional Trials (SPIRIT) [10] guidelines (see Additional file 1). Ethics approval has been obtained from the Alfred Hospital (526/14) and Monash University (CF15/1306 - 2015000623) Human Research Ethics Committees.

### Participants

A total of 170 individuals with chronic low back pain and lumbar disc herniation will be recruited through (i) general practitioners, medical specialists and allied health professionals; (ii) advertising on social media (including Facebook), and in community magazines and national newspapers; and (iii) posting of flyers in community locations such as shops, libraries and medical clinics. Written informed consent will be obtained from all participants by research staff trained in study procedures specific to this trial.

### Inclusion criteria

We will recruit male and female participants aged 18–60 years with chronic low back pain, which is defined as pain between the lower borders of the rib cage and the gluteal folds that has been present for greater than 3 months [11, 12] and with the presence of a disc herniation on magnetic resonance imaging (MRI).

### Exclusion criteria

Participants with any of the following will be excluded: (1) specific pathological entity, such as infection, metastasis, osteoporosis or fractures; (2) any contra-indication or allergy to antibiotic therapy; (3) antibiotic therapy in the past 3 months; (4) a compromised immune system; (5) osteomyelitis; (6) any kidney disease; (7) planned surgery in the next 6 months; (8) major co-existing illness which might confound the assessment of function; (9) another significant musculoskeletal condition; (10) pregnancy, planning or trying to become pregnant or breast feeding; or (11) inability to give informed consent, including individuals that are unable to read, speak or understand English.

### Randomisation and blinding

Randomisation will be performed by a computerised random number generator that will be held by an independent researcher not involved in other aspects of the trial. Allocation concealment will be ensured by the use of a central automated allocation procedure, with security in place to ensure allocation data cannot be accessed or influenced by any person.

The randomised controlled trial will be double-blinded, with both participants and investigators assessing outcomes blinded to treatment allocation. Allocation concealment and double blinding will be ensured by (1) the medications being dispensed by a Therapeutic Goods Administration licensed facility which specialises in product manufacturing of investigational products for the pharmaceutical industry, (2) the use of a placebo tablet that is identical in appearance and (3) questionnaires that are administered by research assistants blinded to group allocation.

### Intervention

Participants in the intervention arm will receive the antibiotic, amoxicillin-clavulanate (coamoxiclav; 500 mg/125 mg) tablets (Aspen Pharmacare Australia, NSW), two times per day for 90 days, and those in the control group will receive microcrystalline cellulose tablets, which will be identical in size, colour, coating and packaging to the active tablets. We selected amoxicillin-clavulanate for several reasons: (i) it is widely used in clinical practice; (ii) the initial clinical trial by Albert et al. found amoxicillin-clavulanate to have a beneficial effect on chronic low back pain with disc herniation and Modic changes type 1 [6]; (iii) our systematic review of biopsy studies showed that a variety of bacteria are present in the spinal disc and a broad-spectrum antibiotic, such as amoxicillin-clavulanate, is needed [8]; and (iv) there is evidence that it can penetrate the spinal discs [13]. All participants will be provided with usual care by their treating health practitioners.

### Study procedure

The study procedures are presented in Fig. 1 and Table 1. Potential participants will be initially screened over the phone using a questionnaire to determine whether they meet the eligibility criteria. They will then attend an initial assessment at Monash University Department of Epidemiology and Preventive Medicine in Melbourne (State of Victoria, Australia) with the aim of obtaining informed consent and further examining the individual’s eligibility to participate in the trial. A full blood examination (FBE) and electrolyte and liver function tests will be performed to exclude conditions such as liver impairment or renal failure, and a c-reactive protein (CRP) blood test will be performed to detect inflammatory conditions such as osteomyelitis. A lumbar spine MRI will also be performed at baseline to determine whether a disc herniation is present and allow for the assessment of Modic changes. The trial will not involve collecting biological specimens for storage.

**Fig. 1 Fig1:**
[figure not shown]
Trial flow diagram

**Table 1 Tab1:**
[figure not shown]
Schedule of enrolment, interventions and assessments

*Adverse events were assessed with a blood test at additional time points not presented in this table; including 2 and 6 weeks to monitor liver function and any other adverse events

Eligible participants will be randomised, asked to complete the baseline questionnaire and sent the first 3 months of amoxicillin-clavulanate or placebo, followed by the second 3 months half way through the trial. A blood test will be performed at 2, 6 and 12 weeks to monitor liver function and any other adverse events. Participants will also be requested to report any adverse events to the research staff spontaneously. Details of major adverse events and their relationship with study intervention will be recorded and reported to the ethics committees. If participants experience adverse events as a result of this research project, appropriate medical treatment will be provided to participants. All participants’ physician will be notified of their inclusion in the trial.

Participants will be contacted at 3, 6, 9 and 12 months to continue to monitor any side effects of the treatment and collect outcome data. A lumbar spine MRI will be conducted at 12 months to assess the presence of Modic changes. The same researchers, who are blinded to treatment allocation, will measure all clinical variables, administer questionnaires, monitor compliance and record adverse events. Unblinding will be allowed under certain circumstances, such as a participant’s doctor requiring their allocated intervention to ensure they receive the appropriate medical care. Compliance by trial medication will be assessed by pill count. Participants will not be paid for their participation in the trial, but they will be reimbursed for parking and transport costs.

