### Statistical analysis

Summary statistics comparing randomised arms at baseline will be tabulated. Intention-to-treat analyses of primary and secondary continuous outcomes will be performed by linear regression adjusting for the baseline of the outcome variable. Logistic regression will be performed for binary outcomes. Adjustment for imbalanced baseline factors, including the presence of symptoms other than low back pain, will be performed as supplementary analyses. We will perform a per-protocol analysis as a secondary analysis, defining compliance to the protocol as taking ≥ 80% of the planned number of pills, which is consistent with methodology from a previous trial [7]. Analysis of the moderating effect of Modic change status will use regression models with an interaction term between intervention arm and Modic change status, and adjusting for baseline values of the outcome variables. Missing outcome data for all analyses will be imputed via multiple imputation methods using relevant baseline and post-baseline measurements.

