	No other treatment allowed during the 1 year trial period.	Usual care allowed Encouraged to limit non-steroidal anti-inflammatories	Usual care allowed Use of non-opioid analgesia and non-steroidal anti-inflammatories permitted

We have chosen to examine the efficacy of amoxicillin-clavulanate in our clinical trial as it is a broad-spectrum antibiotic, with clavulanic acid also having an antibacterial effect. This is based on our systematic review, which found that of the 9 studies that examined spinal disc material, 8 reported the presence of more than one bacteria, and *Cutibacterium acnes* and *CN staphylococci* were found to be the most prevalent [8]. Given the question of whether antibiotics are effective for low back pain remains unanswered and amoxicillin-clavulanate was used in the study by Albert et al. and found to have a beneficial effect [6], we wanted to avoid the potential limitation that our antibiotic coverage was inadequate. Moreover, while there is potential for side effects, in particular liver injury, with the use of amoxicillin-clavulanate, the risk is extremely low (21 cases of liver failure in 28 years) [26] and will be significantly minimised in our trial by excluding those with a risk factor for liver injury and ensuring regular monitoring with blood tests during the treatment period. In addition, we chose to investigate the efficacy of amoxicillin-clavulanate for a 3-month period, as the study by Albert et al. used amoxicillin-clavulanate for 100 days and found a beneficial effect [6], and our patient subgroup is considered to be similar to a low-grade vertebral osteomyelitis, which is commonly managed with antibiotic therapy for similar treatment durations (4–6 weeks to 6 months).

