
This trial has several potential limitations that need to be considered. Given we are examining the effectiveness of amoxicillin-clavulanate, which is a broad-spectrum antibiotic, it is not possible to extrapolate the findings to other types of antibiotics. The potential for adverse events is an important consideration with the use of amoxicillin-clavulanate for a 3-month period. We will record the type, frequency and severity of adverse events that occur during the trial. However, the current study is not designed to comprehensively evaluate adverse events; to determine this, prospective cohort studies with larger sample sizes are needed. Antibiotic resistance is an important issue, which is highlighted by the World Health Organisation’s statement that antimicrobial resistance is a global threat to health which needs urgent action at the highest political level [27, 28]. While there is potential for benefit for individuals with low back pain, the potential for harm with the inappropriate use of antibiotics is also significant. If there is growing evidence to show the effectiveness of antibiotic treatment for the management of back pain, investigation in future trials is paramount.

Low back pain is a major global health problem [1], and there is an urgent need for effective, evidence-based treatments [2]. While there is huge interest in the potential effectiveness of antibiotic treatment for chronic low back pain with disc herniation, two clinical trials have reported conflicting results [6, 7]. Thus, the efficacy of antibiotic therapy for chronic low back pain and the patient subgroup that may benefit is still unknown. This clinical trial will provide high-quality evidence to determine whether amoxicillin-clavulanate is effective for the management of low back pain with disc herniation. If amoxicillin-clavulanate is found to be effective, it could be used to reduce pain and disability in individuals with chronic low back pain and, in turn, reduce the huge burden associated with this condition.

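### The Study procedure text sends participants two 3-month supplies of study drug, which contradicts the single 90-day (3-month) course stated everywhere else

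*Protocol article*

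**What the plan says.** Five places in the protocol article describe one course of about three months.

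- Abstract, Methods: "amoxicillin-clavulanate (500 mg/125 mg) twice per day for 90 days or placebo".
- Methods, Intervention: "two times per day for 90 days".
- Discussion, Table 2: 3 months in this trial's own column.
- Discussion, on the choice of antibiotic: "we chose to investigate the efficacy of amoxicillin-clavulanate for a 3-month period".
- Discussion, on limitations: "the use of amoxicillin-clavulanate for a 3-month period".

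One place differs. Under Methods, Study procedure (text below Table 1), randomised participants are "sent the first 3 months of amoxicillin-clavulanate or placebo, followed by the second 3 months half way through the trial".

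Three other statements depend on how long treatment lasts.

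- Statistical analysis defines per-protocol compliance as taking at least 80% "of the planned number of pills". The number is not given. Study procedure says compliance is measured by pill count.
- Study procedure states: "A blood test will be performed at 2, 6 and 12 weeks to monitor liver function and any other adverse events". The Adverse events section gives the same three time points.
- The Discussion says the risk of liver injury is reduced partly by "ensuring regular monitoring with blood tests during the treatment period".

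Study procedure also provides for contacts at 3, 6, 9 and 12 months to follow up side effects. The Economic analysis section counts the cost of the antibiotic.

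**The concern.** The Study procedure sentence names the study drug and placebo, so it cannot refer to questionnaires or follow-up visits. It describes two consignments of three months each, about six months of tablets. No reading of it fits a single 90-day course, and nothing in the visible text explains the difference. Its timing is also unclear: half way could mean month 3 of a six-month course, or month 6 of the 12-month follow-up, which would leave a gap in dosing.

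The planned amount of study drug is a core design fact, and the article exists partly to compare this trial with an earlier 100-day trial and an earlier 3-month trial. Until the conflict is settled, four things have two or more possible values:

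- the denominator of the per-protocol rule;
- the planned drug cost in the economic evaluation;
- the interval between last dose and the primary outcome;
- whether the blood-test schedule matches the Discussion's description of it.

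**Working it through.** The document states no planned tablet count, so there is no figure of its own to reproduce on this point. The one related figure is the sample size, checked here only to show that it does not depend on treatment length. With SD 3.0, a difference of 1.5 units, 90% power and two-sided alpha 0.05 (alpha is assumed, as the article does not give it), n per arm = 2 × (1.960 + 1.282)² × (3.0 / 1.5)² = 84.1, rounded up to 85. This agrees with the stated 85 per arm, and no term in it involves tablets or duration.

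**Inputs.** Two tablets per day and 90 days (Intervention); two supplies of 3 months (Study procedure); an 80% threshold (Statistical analysis); last scheduled blood test at week 12 (Study procedure and Adverse events); primary outcome at 12 months (Primary outcome measures). Assumption: the twice-daily schedule is unchanged in any second supply. Two 3-month supplies are taken as 180 to 183 days.

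**Planned tablets and per-protocol cut.** Planned tablets = 2 × days; cut = 0.80 × planned tablets.

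| | One 90-day course | Two 3-month supplies |
|---|---|---|
| Planned tablets | 2 × 90 = 180 | 2 × 180 = 360 (up to 2 × 183 = 366) |
| 80% cut | 0.80 × 180 = 144 | 0.80 × 360 = 288 (up to 0.80 × 366 = 293) |
| Compliance of a participant taking 180 tablets | 180/180 = 100% | 180/360 = 50% (180/366 = 49%) |
| Compliance of a participant taking 144 tablets | 144/180 = 80% | 144/360 = 40% (144/366 = 39%) |

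A participant who takes every tablet of a 90-day course is inside the per-protocol set on one denominator and well outside it on the other.

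**Last dose to the 12-month outcome.**

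- One course ending at month 3: 12 − 3 = about 9 months.
- Second supply starting at month 3 and ending at month 6: 12 − 6 = about 6 months.
- Second supply starting at month 6 and ending at month 9: 12 − 9 = about 3 months.

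**Blood-test coverage.** The last scheduled test is at 12 × 7 = day 84. For one course, 84/90 = 93% of treatment days have passed by then. For two supplies, 84/180 = 47% of tablet-days (84/183 = 46%). On either start date for a second supply, day 84 falls before it begins, so no listed test falls within it. The side-effect contacts at 3, 6, 9 and 12 months continue on every reading.

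**Drug cost.** At a fixed price per tablet, the planned antibiotic cost per participant scales as 360/180 = 2. The article gives no price, so this cannot be turned into money.

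**The case against.** The strongest reply is that this is one stray sentence. Every other statement of duration says 90 days or 3 months, the Discussion argues for three months, and blood tests ending at week 12 fit a 90-day course. The Monitoring section says the trial will stop if metformin has unacceptable side effects. Metformin is not a treatment in this trial, so some text may have been carried over from another protocol, and the supply sentence may share that origin. This is a fair inference and it lowers the likelihood that two regimens were ever in use. It does not settle the matter: the sentence stands in the operative Methods text, and the trial flow diagram and Table 1, which might resolve it, are not shown.

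The second reply is that little analysis depends on it. That stands for the primary comparison, which is by intention to treat. The per-protocol analysis is secondary, and a total tablet count could properly sit in the full protocol or the statistical analysis plan. The point here is that the article gives two conflicting durations from which to derive that count, and not that the count is missing.

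A reader might infer three stronger things, none of which the document supports.

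- *That duration, denominator and safety window are each defined two ways.* Only duration is. The denominator is stated once, and the blood-test schedule is stated consistently in two sections.
- *That participants received twice the intended drug, or took a second supply without laboratory monitoring.* The article is not a dispensing instruction. Medication is dispensed by a licensed facility, and the article cites protocol version 4 of 16 March 2018. The monitoring gap exists only if a second supply was part of treatment.
- *That the last dose would fall only three months before the endpoint.* This holds only if a second supply starts at month 6; a month-3 start gives about six months.

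**Conclusion.** The text is wrong as written: its two accounts of how much study drug participants are sent cannot both hold. The direct contradiction is confined to treatment length. Its main statistical consequence is that the per-protocol cut is either 144 tablets or about 288 (up to 293), so that a full 90-day taker is 100% or about 50% compliant. The planned antibiotic cost could differ by a factor of two, and the interval from last dose to endpoint is about 9, 6 or 3 months. The Discussion's description of blood monitoring fits a 90-day course closely, but would not fit a second supply.

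These sizes assume an unchanged twice-daily schedule and, for the intervals, the stated start times. The intention-to-treat primary analysis and the sample size are unaffected. The supply sentence may be a drafting error, but the document cannot show this. No view is taken on which duration or monitoring schedule is right.

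**What to change.** Reconcile the Abstract, Intervention, Study procedure, Statistical analysis and Discussion (including Table 2) with the approved protocol and the dispensing records. Then:

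- state one supply schedule and one planned tablet count;
- define the 80% per-protocol rule on that count, and fix it before unblinding;
- use the same count for the antibiotic cost in the economic evaluation;
- align the Discussion's description of blood-test coverage with the reconciled treatment period.

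If the records show that supply differed between participants, report this and settle the denominator before unblinding.

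The cost is a text correction and a check of dispensing records. It needs no additional participants and no new trial procedures.
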